Preventing mental illness earlier during development could decrease subsequent mental health-related hospitalizations and suicide attempts. However, prevention poses a tough challenge, as these outcomes are usually the final stage of a series of small breakdowns that happen at several levels in the life course. Considering the multi-causality of the phenomenon, it is important to investigate several social drivers, risks, and protective factors at the individual and contextual level. Poverty, gender and racial inequality are associated with increased mental illness [6] and suicide [7, 8]. This might be explained by increased stress, family difficulties, alcoholism, impulsivity, violence and parental mental illnesses among the poor [3, 9–11]. However, those mechanisms are yet to be fully understood and tested, especially among youth in a LMIC setting.

Brazil has one of the largest mental health-related hospitalizations among youth, and suicide is the third most common reason for death due to external causes, and alarmingly both have increased over the last 13 years. The World Health Organisation (WHO) recommends that suicide prevention should be prioritized on the global public health agenda [12]. However, it remains unclear what interventions are best suited for targeting youth at a population level and what preventive interventions delivered earlier in life have a long-term effect on preventing mental health-related hospitalizations and suicide.

The Brazilian government introduced the Bolsa Familia Programme (BFP) in 2003 [13] to promote social inclusion and strengthen human capital among the poorest. Poverty alleviation programs could influence mental illness by diverse pathways [3, 5, 9] through decreasing income inequalities or by reducing socioeconomic hardship through increased family income, which might result in stress reduction, less family disruption, or decreased alcohol consumption [14]. Therefore, we might expect government poverty alleviation programs such as BFP to have an impact. However, whether this Brazilian government program has impacted, and knowledge of the pathways and mechanism of its impact, on youth mental illness and suicide remains unknown.

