## Study innovation

The Brazilian Cash Transfer Program, “Bolsa Família Program” (BFP), is one of the largest conditional cash transfer programs worldwide, which appears to have had an important public health impact. Studies indicate that BFP has promoted social inclusion and strengthened human capital among the poorest, reducing poverty and inequalities, besides increasing school attendance among youth and reduced violence, factors that are associated with mental health [5, 7, 10, 16]. A recent study found that municipalities with higher coverage of the BFP had lower suicide, indicating that this program may have some reduction effect [7]. However, understanding the impact of this program at the individual and contextual level, analyzing by areas and municipalities, and investigating pathways and mechanisms for preventing mental health-related outcomes remains unexplored. Evaluating the impact of these changes is of great interest for health systems in LMICs such as Brazil, where dramatic socioeconomic changes have taken place in a short time. If Brazilian programs are associated with lower hospitalization from mental illness and suicide, there may be ways to support prevention through increased program coverage and integration with the current mental health strategy.

*First*, this study provides a unique opportunity to use the largest existing longitudinal dataset (The 100 Million Brazilian Cohort) in any LMIC of linked socioeconomic and health individual-level data to assess the effects of socioeconomic conditions and BFP on mental illness and suicide among young people.

*Second*, the longitudinal aspect of the cohort, with a long follow-up period of 18 years of socioeconomic and health data, will allow us to explore and assess in-depth dynamics, lagged and long-term effects of changes in living conditions, parents’ mental illness and in exposures to BFP. The long-term impact of BFP on a diverse population once such a program has been scaled up and sustained for over a decade is completely unknown.

*Third*, with this project, we will be able to identify risk factors for mental health-related hospitalizations and suicide (such as demographic factors, economic factors, parents’ underlying mental illness and substance use disorders) and investigate pathways and mechanisms using a linkage of massive datasets covering half of the country for sociodemographic information and the full country for hospitalization and mortality information.

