Notifiable Diseases Information System (SINAN)	This dataset comprises compulsory notifiable diseases information and violence, emotional and physical, as well as suicide attempt.	Compulsory notifiable diseases, including occurrences reported for: self-inflicted violence (333,933), interpersonal violence (2,111,051), and intimate partner violence (433,664).	Individual sociodemographic and clinical data of suspected and confirmed cases of interpersonal and self-inflicted violence (suicide attempt and self-agression) and intimate partner violence. It also includes information regarding the perpetrator, such as relationship with the victim.
Demographic Census (IBGE)	Household census to collect information on all households and individuals in the country and characterize the Brazilian population in terms of its demography and socioeconomic characteristics.	All Brazilian municipalities (n = 5,670).	Population, fertility, mortality, migration, housing characteristics, characteristics of the neighbourhood, education, income, labour, social inequality (Gini index), Human Development Index (HDI), proportion of poor people, etc.

Besides information from BFP, from the CadÚnico, we will also access information from the Hospitalization Information System to identify hospitalizations from: (A) mood disorders (832,974); (B) anxiety; (C) psychosis (1,952,605); (D) prescribed or illicit drug abuse and dependence; (E) alcohol abuse and dependence; (F) alcohol-related liver, problem/chronic liver disease; (G) physical injuries (228,278); (H) attempted suicide (178,606); and (I) suicide (181,527), from 2001–2018. As well as violence notifications from the Brazilian Notification System for Health Surveillance and all cause-specific mortality data, collected from the Brazilian Mortality Information System. All hospitalization, notification, and mortality information data were obtained from the DATASUS held by the Brazilian Ministry of Health and transferred to CIDACS [29] for research purposes. All the data are recorded in the three systems using the International Classification of Diseases, 10th revision. Information systems have improved considerably in Brazil; an analysis of the adequacy of mortality data from 2003 to 2005 found high quality and reliable information [30]. All the data available at CIDACS/FIOCRUZ covers a period from 2001–2018; however, we may access more recent years when the study begins.

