We will apply methods from the SEM group, to specify and test the paths laid out in Fig 1. SEM will be used to fit models to the specifications in Fig 1 to allow a judgement on which models best fit our data, therefore allowing the identification of the model, which might be the closest to the causal paths underlying the relationship between exposure and outcome, including potential confounders. Estimation is performed either by Maximum Likelihood. Besides identification of the best fitting models, SEM allows detailing the relationship between indicators (variables) included in the models. After deciding which models are optimal, the particular coefficient estimates are calculated, which can be of fundamental importance to the identification of the intermediate nodes that have the highest influence on the outcome, or which act as mediators or moderators. Mediators are useful representations of confounders, and as long as the path coefficients are calculated, one can precisely estimate the effects resulting from the mediator.

Aim 4: Investigate early life exposures, intergenerational aspects, and to forecast scenarios in Brazil until 2030 using microsimulation models.

Finally, to match this aim we will examine: timing of the intervention in the life course, e.g., if cash transfer delivered earlier in life (e.g., in 2004 when an adolescent was 14 years old) will be associated with lower mental health-related hospitalizations and lower suicide rates 10 years later (when the same adolescent will be 24 years old); and whether mental health-related problems such as suicidality, post-traumatic stress disorder (PTSD), violent behavior passes over to second generations; and, furthermore to forecast scenarios of mental health-related hospitalizations and suicide rates using microsimulation models. This will leverage the results from previous objectives and compare the impact of different BFP implementations on mental health-related hospitalizations and suicide in Brazil until 2030.

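### The models named for Aim 4 do not contrast early with late entry to BFP, and data for 2003–2018 cannot link early-childhood entry to outcomes at ages 20–24

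*Protocol article*

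**What the plan says.** All references are to the protocol article.

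- **Aim.** Aim 4 under Analytic strategy is to "Investigate early life exposures, intergenerational aspects, and to forecast scenarios in Brazil until 2030 using microsimulation models". Its first sub-question is about timing: "if cash transfer delivered earlier in life (e.g., in 2004 when an adolescent was 14 years old" is associated with fewer hospitalizations and "lower suicide rates 10 years later (when the same adolescent will be 24 years old". These are the only ages the aim names, and they are given as an example. No age range defines early life.
- **Models.** The paragraphs that follow name two models for this sub-question. One is an extended Cox model for recurrent hospitalizations, with receipt or non-receipt of the programme as the contrast. The other is a longitudinal logistic model with age as the time variable. Start age is not named as an exposure in either.
- **Programme start.** Background: "The Brazilian government introduced the Bolsa Familia Programme (BFP) in 2003".
- **Data window.** Data and measures, text after Table 1: the data held "covers a period from 2001–2018; however, we may access more recent years when the study begins".
- **Length of data.** Study innovation describes a cohort "with a long follow-up period of 18 years of socioeconomic and health data, will allow us to explore and assess in-depth dynamics".
- **Trend.** Background says of youth mental-health hospitalization and suicide that "alarmingly both have increased over the last 13 years".

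**The concern.** The question is about when in life the transfer arrives. The stated contrast is about whether it arrived at all. A received-or-not coefficient averages over all entry ages, so it cannot say whether entry at 5 does more than entry at 14. Using age as the time scale deals with attained age, not with age at entry.

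The window also removes part of the question. If a reader takes the early-life aim to include early childhood, and takes the outcome ages to include the early twenties, no one in the data links the two.

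Two natural ways of filling the gap would mislead:

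- Carrying the example's ten-year lag across start ages would compare people at different attained ages.
- Fixing attained age and using families who entered at launch would place younger starters in later calendar years, when by the protocol's own account background rates were higher.

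These can push the estimate in opposite directions, so the choice of time anchor could affect the sign. The retrospective estimates also feed the forecast to 2030, where people exposed from birth do reach their twenties.

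**Working it through.** **Inputs.** Programme start 2003 (Background; month not given). Last data year 2018 (Data and measures). Example: start at 14 in 2004, outcome ten years later at 24 (Analytic strategy, Aim 4).

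**1. The plan's own example.** 14 + 10 = 24 and 2004 + 10 = 2014. That is four years inside the window, so the example is feasible. Starts at 14 can be read at 24 for start years 2003 to 2018 − 10 = 2008, which is six start years (births 1989–1994).

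**2. Longest exposed follow-up.** 2018 − 2003 = 15 years.

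**3. Lowest start age observable at attained age A.** This is A − 15 in whole years. Exact birthdays can lower it by one: a person born in late December 1994 was 8 for nearly all of 2003 and turned 24 at the end of 2018.

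| Attained age | Lowest start age (whole years) |
|---|---|
| 15 | 0 |
| 18 | 3 |
| 20 | 5 |
| 24 | 9 |

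Start age 9 read at 24 exists only for start year 2003 and birth year 1994.

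**4. Highest attained age by start age s.** This is s + 15: a start at 0 is followed to 15, at 5 to 20, at 9 to 24. Starts at 0–4 therefore give essentially no observation at 20–24.

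**5. If later years are linked (assumed end years).** The age-24 floor is 24 − (end year − 2003): 2019 gives 8, 2020 gives 7, 2021 gives 6, 2022 gives 5. Following a start at birth to 24 needs data to 2003 + 24 = 2027.

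**6. A ten-year lag applied across start ages.** A start at 4 is read at 4 + 10 = 14; a start at 14 is read at 24. Start age and attained age then move together.

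**7. Fixed attained age, launch entrants only.** Outcome year = 2003 + (attained age − start age). For an outcome at 18, a start at 3 is read in 2018 and a start at 14 in 2007. The size of any resulting bias cannot be computed, because the article gives no rates by year.

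**8. How far start age is bound to calendar year.** With the outcome at 24, start year 2004 still admits start ages 10 to 23. Over the 120 feasible start-age by start-year cells, equally weighted, the correlation is 0.50. But start age = start year − birth year exactly, so a design with intercept, start age, start year and birth year has rank 3 of 4. The tie is partial across birth cohorts and complete within one.

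**9. The forecast.** People born in 2003–2006 turn 24 in 2027–2030 and could have been exposed from birth. The 2001–2018 data contain no such person at 24.

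**The case against.** The strongest reply is that the plan promises less than the concern assumes. Several stronger readings are tempting, and the document does not support them:

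- **That the question cannot be answered at the ages named.** The named ages are 14 and 24, and that contrast fits the window.
- **That a ten-year lag is the rule.** It is introduced as an example, and neither model fixes a lag or restricts outcomes to 24.
- **That 18 years of exposure are claimed.** The 18 years describe the span of the data, pre-programme years included.
- **That 2018 is a hard limit.** The article says more recent years may be accessed.
- **That start age is fixed by calendar year.** This is exact only within a birth year.
- **That effects of preschool entry on outcomes at 20–24 are promised.** Early life is left undefined, and the one illustration is an adolescent.

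It is also fair that calendar-period or cohort terms may be left to a fuller analysis plan; their absence is not counted here.

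All of this stands, and it limits the point. It does not remove it. The article does state the exposure contrast for the timing question, and that contrast does not test timing. No analysis plan can create observations outside the window, and later linkage helps only slowly (step 5).

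**Conclusion.** The point holds in a limited form. As described, the Aim 4 models do not test timing of entry. With entry from 2003 and data to 2018, exposed follow-up is at most about 15 years. Early-childhood entry can be studied only up to the mid or late teens: about 15 for a start at birth, about 19 for a start at 4. Outcomes at 20 need a start at about 5 or later, and at 24 a start at about 9 or later.

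This assumes that families could receive BFP from 2003; a first receipt in 2004 would raise each floor by one year. It also assumes that 2018 remains the last year, and that ages are counted in whole years, with exact birthdays lowering each floor by at most one.

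The adolescent example is sound, so this is not a fatal flaw in Aim 4. It is a worthwhile and inexpensive correction to the contrast and to the reach of the early-life claim.

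**What to change.** 1. Define the timing analysis by start-age band and attained-age band, with a table of the cells the window supports, and limit early-life conclusions to those cells.
2. Make age at entry the exposure. Compare early and later entrants of the same birth year at the same attained age. Outcome year = birth year + attained age, so this fixes the outcome calendar year without a further adjustment.
3. State that within a birth year start age and start year cannot be separated, so an early-entry effect is also an effect of entering in an earlier programme year.
4. Do not carry the example's ten-year lag across start ages.
5. Label any forecast effect of early-childhood receipt on outcomes at 20–24 as extrapolation.
6. Keep the 18 years as the data span, and add that exposed follow-up is at most about 15 years. Update the table if later years are linked.

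The cost is rewording Aim 4 and one table from data already held. The downside is a narrower claim, with no early-childhood conclusion for ages 20–24 until enough later years are linked.

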**Fig 2 pone.0272481.g002:**
[figure not shown]
Flowchart of non-beneficiary (non-BFP) and beneficiary of the Bolsa Familia Program (BFP) to test the association between BFP and youth mental health-related hospitalizations and suicide.

**Table 1 pone.0272481.t001:** Summary of the dataset’s description, from 2001 to 2018.

Dataset	Description	Sample	Variables of interest
The 100 Million Brazilian Cohort Baseline^70,73^	It was built from socioeconomic and demographic information of individuals applying for social benefits in Cadastro Unico (CadÚnico). CadÚnico is an extensive questionnaire with information on the household and on each individual.	114 million Brazilian cohort, including 66,079,181 Bolsa Familia Program beneficiaries and 47,928,524 non-beneficiaries. Among them 41,764,126, youth aged from 5–24 years old in the day of registration.	Demographic and socioeconomic variables (sex, age, ethnicity, education, work), conditions of the household (type of residence, material of household, household density, household supply, garbage destination etc), Health Care utilization, Institutional and community support (participation in groups, access to Social Assistance Reference Center, etc.) and Brazilian government social protection programs (BFP, etc).
Mortality Information System (SIM)^74,75,72^	The national system aimed to collect information on all deaths in Brazil death certificates. All deaths are recorded using a national standardized form and causes of death are registered according to the updated International Classification of Diseases CID-10.	All mortality cause (n = 21,313,290), including suicide (n = 181,527).	Demographic and socioeconomic variables (sex, age, ethnicity, education, work), place the death took place and primary and secondaries causes of death.
Hospital Information System (SIHSUS)^1^	All hospitalizations admissions financed by the Brazilian National Health System are recorded in this system. It includes about 80% of the Brazilian populations, approximately 150 million people	Hospitalizations from mental illness 5,478,980, including: 1,698,663 from alcohol and substance use-related disorders; 1,952,605 from schizophrenia; 832,974 due mood disorders, etc.	Identification and qualification of the patient, procedures, examinations, and medical acts performed, diagnosis, reasons for discharge, amounts due etc.

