#### Analytic strategy

Aim 1: To use large national datasets to evaluate the effect of a broad range of social drivers and of a social-economic intervention on youth mental health.

In this step we will evaluate: first the effect of the BFP and social drivers such as family income, poverty, early marriage, housing characteristics, family income, parents’ divorce, family composition, and parents’ substance misuse on youth hospitalization from: (A) mood disorders; (B) anxiety; (C) psychosis; (D) prescribed or illicit drug abuse and dependence; (E) alcohol abuse and dependence; (F) alcohol-related liver, problem/chronic liver disease; (G) physical injuries; and (H) attempted suicide and (I) suicide. We will also evaluate if a family history of violence, suicide and psychiatric disorders will be associated with an increased risk of been hospitalized from a mental illness or been a suicide victim among youth. Also, if the BFP reduced the recurrence of mental health-related hospitalizations.

We will run regressions to evaluate the association between important social drivers listed above on mental health-related hospitalizations and suicide among youth in Brazil from 2001 to 2018. Multivariate regression models based on a hierarchical analysis approach will be adjusted for mental health care access, income, location of residence (urban/rural), household living conditions including household density, water supply, sewage and garbage collection, residency type and building material, and stratified by age groups, sex and race. The hierarchical models will be ordered according to the level that they act on the dependent variables (mental health hospitalizations and suicide). It is argued that mental health is conditioned by a series of proximal and intermediate factors, conditioned by socioeconomic situation, among which level of education, marital status, race, home conditions, region, and place of urban/rural residence, all considered social drivers.

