To answer the above sub-objectives, we propose the use of modeling for longitudinal data, since the events are observed over time. For sub-objective firstly we will apply extended Cox model [33], known as a marginal model for multiple or recurring events, to estimate whether the number of hospitalizations related to mental health increases or decreases in the course of life given whether the individuals received the intervention or not [34]. Secondly, we will run logistic regression models for longitudinal data [35] considering the age variable as a temporal measure, in which the outcome will correspond to a new binary variable in relation to having reduced or not hospitalization related to mental health (Yes/No). Regarding the intergenerational effect (sub-objective 2) on mental health issues, we will verify the influence of the parent’s mental health status on the child’s mental health through usual regression models, in which the outcome corresponds to the child’s mental health variable. Besides, we must consider a possible dependency between individuals in the same family. In this case, we will apply mixed models [36] to address the possible intra-individual correlation. All approaches will be validated using appropriate diagnostic and testing techniques.

The third stage of modelling will integrate the datasets and analyses above with Microsimulation Models (MS). Microsimulation is increasingly used in epidemiology and is useful to evaluate both overall and subgroup impacts of public policies [37] This is because microsimulation allows modelling of individual-specific characteristics and associated probabilities of outcomes, and when both are derived and retain the information of an existing retrospective dataset, the original correlation structure between variables and non-linear effects can be taken into account [37]. The MS integration is useful in our case, as both the heterogeneity and dynamic interactions of the population are relevant for the outcome under study. One co-investigator has developed microsimulation studies on the effect of economic crisis and BFP implementation scenarios in Brazil [38, 39] loping a platform for integration of these retrospective data and evaluations with microsimulation models for several health-related outcomes for the 100 Million Brazilian Cohort. A representation of the proposed MS model is presented in Fig 3. For the construction of this MS model, we will adopt a 2-step approach:

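### The Aim 4 yes/no outcome of reduced hospitalization is undefined for youth never admitted and, depending on how they are counted, can mask or reverse a preventive effect

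*Protocol article*

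**What the plan says.** Under Analytic strategy, Aim 4, the first sub-objective is whether cash transfer received earlier in life "will be associated with lower mental health-related hospitalizations and lower suicide rates 10 years later". Two models are named for it.

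- An extended Cox model for recurrent events, "to estimate whether the number of hospitalizations related to mental health increases or decreases in the course of life", according to whether the intervention was received.
- A logistic model for repeated observations, with age as its time axis. Its dependent variable is described as follows: "the outcome will correspond to a new binary variable in relation to having reduced or not hospitalization related to mental health (Yes/No").

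For the logistic outcome the text does not say what the reduction is measured against, who enters the model, or how a youth with no admissions is scored. The cohort row of Table 1 describes the youth population: "Among them 41,764,126, youth aged from 5–24 years old in the day of registration". Aim 4 states no restriction to previously hospitalized youth. Aim 1 asks separately "if the BFP reduced the recurrence of mental health-related hospitalizations", but does not link that question to this model.

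**The concern.** A reduction is a change within one person, and it can occur only if there was an admission to begin with. The sub-objective instead compares the level of later hospitalization between youth with and without earlier transfer. The two differ most for the youth whom the programme is hoped to benefit: those who never have a first admission. On a yes/no scale they have no natural code. Scoring them as not reduced puts them with youth whose admissions stay high. Scoring them as reduced credits a fall that never took place. Dropping them removes prevention of first admissions from the analysis.

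Among youth who do have an earlier admission, regression to the mean makes a fall likely with or without the programme. If that admission came after receipt began, the programme may itself have affected who is in the group.

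At stake is the direction of one of the two results for this sub-objective. The two models could disagree because of how this variable is built and not because of anything in the data.

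**Working it through.** The protocol article gives no effect size, power or expected odds ratio for this model, so there is no figure of its own to reproduce.

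**1. How many have nothing to reduce.** The Hospital Information System row of Table 1 gives "Hospitalizations from mental illness 5,478,980" over 2001–2018 and coverage of "approximately 150 million people".

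- 5,478,980 / 150,000,000 = 3.65%. Readmissions are counted repeatedly, so this is an upper bound on the share ever admitted. At least about 96% were never admitted.
- These are all-age national counts, and applying them to cohort youth is an assumption. As an extreme check, suppose every one of these admissions belonged to a different cohort youth: 5,478,980 / 41,764,126 = 13.1%. Even then about 87% would have none.

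**2. Direction if never-admitted youth count as not reduced.** The inputs here are assumptions, not figures from the documents. There are two consecutive intervals. The risk of admission in the first is p = 0.02 without the programme. The probability that someone admitted in the first interval is admitted again in the second is r. The programme multiplies both by 0.8, so it acts in both intervals. Reduced means admitted in the first interval and not in the second:

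P(reduced) = p(1 − r), and OR = [P1/(1 − P1)] / [P0/(1 − P0)], where 1 is with and 0 is without the programme.

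| Readmission r without programme | P0 | P1 | OR for reduced |
|---|---|---|---|
| Independent intervals (r = p) | 0.02 × 0.98 = 0.0196 | 0.016 × 0.984 = 0.01574 | 0.80 |
| 0.3 | 0.02 × 0.70 = 0.0140 | 0.016 × 0.76 = 0.01216 | 0.87 |
| 0.4 | 0.02 × 0.60 = 0.0120 | 0.016 × 0.68 = 0.01088 | 0.91 |
| 0.6 | 0.02 × 0.40 = 0.0080 | 0.016 × 0.52 = 0.00832 | 1.04 |

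The direction changes where 0.8(1 − 0.8r) = 1 − r, that is 0.36r = 0.20, so r ≈ 0.56. The documents give no readmission rate.

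**3. Same coding, reference interval before the programme.** Now p is 0.02 in both groups and only r is multiplied by 0.8.

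- Independent intervals: 0.02 × 0.984 = 0.01968 against 0.0196, OR 1.00.
- r = 0.3: 0.02 × 0.76 = 0.0152 against 0.0140, OR 1.09.
- r = 0.4: 0.02 × 0.68 = 0.0136 against 0.0120, OR 1.14.

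There is no reversal, though with little readmission the effect nearly vanishes.

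**4. A second model as a check.** Admissions in two windows were taken as Poisson counts with mean 0.002 to 0.2 per window, with no frailty or with shared gamma frailty of shape 0.5 or 0.1. The true rate ratio was 0.8, and reduced meant fewer admissions in the second window than in the first.

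| Handling of never-admitted youth | Where the programme acts | OR for reduced |
|---|---|---|
| Not reduced | Both windows, ×0.8 | 0.80 to 0.90 |
| Not reduced | ×0.9 in the first, ×0.8 in the second | 0.90 to 1.01 |
| Not reduced | Second window only | 1.00 to 1.12 |
| Reduced | Any of the above | 1.13 to 1.28 |
| Excluded: only youth admitted in the first window | Any of the above | 1.08 to 1.35 |

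One and the same programme effect thus gives odds ratios from 0.80 to 1.35, depending on choices that the outcome wording leaves open.

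**5. The alternative outcome.** Take any admission in an interval, with risks 0.016 and 0.020: OR = (0.016/0.984) / (0.020/0.980) = 0.80 for admission. This is the correct direction, and never-admitted youth are simply non-events.

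**The case against.** The strongest reply is that the article never says how never-admitted youth are coded, or that they enter this model at all. A reader might infer that they are scored as failures and that an effective programme would therefore appear harmful. The documents support neither step. Reversal needs that coding and also a protective effect already present in the reference interval. A before-and-after reading of reduction, a different coding, or a risk set of previously admitted youth gives a null or correct-direction result. Even under the unfavourable coding, the direction depends on an unknown readmission rate. All of this stands, and the point is worded conditionally for that reason.

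A second reply is that windows, risk set and derivation rules belong in a full protocol or analysis plan that is not shown. That is right for those details. It does not cover the choice of outcome, which the article states: a within-person reduction is set against a question about levels, and supplying the details later would not make the two match.

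A before-and-after reading is also not a comfortable default here. The article's own example is receipt at 14 and outcome at 24, with age as the time axis, so reference intervals after early receipt would already be exposed.

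Third, the damage is contained. The Cox model for the same sub-objective accommodates youth with no events, and the Aim 1 impact analyses do not use this variable. This also stands, and it limits the severity.

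**Conclusion.** The point holds in conditional form. The stated outcome of the Aim 4 logistic model is undefined for youth with no earlier admission. On Table 1's all-age counts these are about 96% or more of people, and applying that share to youth is an assumption. The outcome does not match the question of whether earlier transfer goes with lower hospitalization.

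If these youth count as not reduced and the programme already acts in the reference interval, a true 20% reduction would give an odds ratio for reduction of about 0.80 to 0.91. This rests on the assumed 2% risk and on readmission between near zero and 40%. Above about 56% readmission the direction is correct again, and with a reference interval before the programme there is no reversal. A certain reversal is not established.

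Severity is moderate: this is one of two models for one sub-objective, and the recurrent-event Cox model is unaffected.

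**What to change.** Define the outcome of the longitudinal logistic model as any mental-health-related admission in the age interval (yes/no), and keep age as the time measure. Never-admitted youth are then non-events in every interval, and an odds ratio below 1 means benefit.

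If an analysis of reduction or recurrence is kept, for example for the Aim 1 recurrence question, restrict it to youth whose index admission precedes receipt of the programme, or a matched index date for non-beneficiaries. Compare youth with similar numbers of prior admissions.

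The first change costs one sentence and uses the same data and model class. The second adds an index-date rule for non-beneficiaries and matching or adjustment on prior admissions.
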